### Criteria for discontinuing or modifying allocated interventions {11b}

At any time during the study, participants may discontinue participation at their personal request without giving any reason or written statement and without incurring any disadvantage. Specific risks or harms to the participant are not expected during study participation. However, participants might experience temporary fatigue due to the length and efforts of the neuropsychological assessments or CT or may feel distressed when confronted with possible deficits during the neuropsychological assessment or CT. Reported adverse events will be recorded and analyzed, and, if necessary, the protocol will be modified accordingly. A travel and residence insurance policy has been taken out for the duration of the study. In general, study allocation will not be modified retrospectively.

### Strategies to improve adherence to interventions {11c}

To improve CT adherence among participants of the EG, various measures are implemented. First, participants of the EG receive printed information on the CT, including their individual CT access data, a step-by-step CT guide including a detailed description of the CT with images, and a brief CT diary. Additionally, participants receive a link via email to access the psychoeducational videos. To give some guidance on how to combine the CT and the videos, participants find a CT and video checklist (similar to Table 1) at the beginning of the CT diary, where they can check off each CT day and video they have completed. Secondly, participants receive printed information on the optional biweekly video consultations led by an unblinded team member (author [name]), including contact details, access information, and times of the sessions. Participants can use these sessions for any CT-related queries, such as for technical problems or questions regarding certain exercises. Finally, and in addition to the previous point, a single team member (author [name]) is in charge of all CT-related tasks, monitors CT progress for all participants to ensure the standardization of all procedures, and functions as the main contact person for participants. In the case that participants do not participate in the CT despite being randomized to the EG (according to their CT data), participants are contacted via telephone (and encouraged to start with the CT).

### Relevant concomitant care permitted or prohibited during the trial {11d}

All participants maintain their usual care routine without any alterations. Only the CT was added to the therapy regimen of the EG.

### Provisions for posttrial care {30}

To date, the administration of CT and neuropsychological assessment has not revealed any adverse side effects, except for occasional signs of tiredness and mild exhaustion. Therefore, no harm is anticipated from CT implementation during the study, and no posttrial care provisions are needed.

### Outcomes {12}

Based on a hybrid type 1 clinical trial design [54], our primary objective is to evaluate the efficacy of the CT. The primary outcome measure is overall cognitive function assessed by the German version of the MoCA [56, 69]. Secondary outcomes include specific cognitive functions, motor, and neuropsychiatric symptoms. Additionally, further patient-reported non-motor outcomes including QoL and ADL were defined. Non-cognitive outcome measures were selected based on recommendations of the International Parkinson and Movement Disorder Society (MDS) and the current German Society of Neurology guideline [70, 71]. CT feasibility and acceptability are also assessed as secondary outcomes. An overview of all outcome measures is shown in Table 2. A more detailed description of the outcome assessment and collection follows in Sect. “Plans for assessment and collection of outcomes {18a}”

**Table 2 Tab2:**
[figure not shown]

[figure not shown]

[figure not shown]
Outcomes, measurement instruments, and timepoints of assessments [56, 61, 72–102]

All items marked with a * are part of the extended version of the established neuropsychological test battery of the Consortium to Establish a Registry for Alzheimer’s Disease (CERAD-Plus) [74–76]

*Abbreviations*: *C**G* control group, *CT* cognitive training, *EG* experimental group

### Participant timeline {13}

Interested individuals undergo a brief telephone screening, in which they receive information on the study purposes and an initial screening for the inclusion criteria. Those meeting the inclusion criteria are invited for baseline assessment, either at the research facility, a room leased specifically for the purpose of the assessment, their home, or a room at a supporting research facility. Figure 2 shows the study design. At baseline assessment, participants first receive detailed written information on the study and are instructed to pose any remaining questions to a trained examiner before providing written informed consent (see Sect. “Who will take informed consent? {26a}”). Following consent, all inclusion criteria are assessed in detail via a checklist. To ensure the exclusion of dementia and severe depressive symptoms, the MoCA and BDI-II are administered, respectively, and scored by the trained examiner before further assessments are undertaken. If inclusion criteria are not met, the assessment is not continued. Eligible participants continue to baseline assessment and, upon completion, are randomized to either the EG or CG (see Sect. “Sequence generation {16a}”). At the end of the baseline assessment, members of the EG receive their printed CT access data, program details (i.e., CT checklist, step-by-step CT guide, and brief CT diary), and a handout with information on the voluntary biweekly video-based consultations either in person or via post to their home by an unblinded member of the study team (author [name]). Additionally, an email is sent to all participants of the EG containing a link with access to the psychoeducational videos, so they can successfully participate in the CT and watch the videos from home. In contrast, those in the CG do not receive any information on the CT but instead are instructed in person, via telephone, or via email by the same unblinded team member (author [name]) to continue their care as usual until the next appointment is agreed upon. According to group allocation, a 5-week CT period (EG) or care as usual (CG) follows, concluding with a post-test at week 7 and a 3-month FU assessment at week 19. These latter assessments are again conducted at a research facility, the participants’ home, or a room leased for the occasion by a blinded examiner.

**Fig. 2 Fig2:**
[figure not shown]
Study design

### Sample size {14}

The a-priori sample size calculation conducted in G*Power 3.1 was based on a meta-analysis [29] reporting a small efficacy of CT on overall cognitive functions. Based on this result, a small effect size is expected for global cognitive functions (*d* ≥ 0.3–0.5). With a power of 80% and a significance level of *p* = 0.05, *n* = 64 participants should be included in each of the two groups. Considering a dropout rate of 10% [38, 44], the sample calculation provided an overall sample size of *n* = 140 participants with each *n* = 70 persons randomized to either EG or CG.

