### Trial design {8}

The study is an ongoing monocentric, single-blinded, two-armed, superiority randomized controlled trial (RCT) with one group of participants (experimental group, EG) receiving a structured digital CT over 5 weeks (four times per week for 45 min) and the other group being a passive wait-list control group (control group, CG), receiving care as usual. In addition to CT, participants in the EG receive access to complementary psychoeducational videos on cognitive health. The study follows a parallel group design. Participants are allocated in a 1:1 ratio to EG and CG. After study completion, the CG will also receive access to CT and psychoeducational videos for ethical reasons. Following good clinical practice, all data will be collected and analyzed in a standardized manner. This protocol adheres to the “Standard Protocol Items: Recommendations for Interventional Trials” (SPIRIT) guidelines.

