## Statistical methods

### Statistical methods for primary and secondary outcomes {20a}

The primary analysis is according to the intention to treat, with no exclusions. The change from baseline in the primary outcome MoCA is analyzed by a linear mixed model for repeated measures (MMRM) with fixed effects for baseline, group, time, and group × time interaction (ARH1-structured variance–covariance matrix over time). The primary comparison at T1 (week 9) is based on a pairwise contrast of estimated marginal means with a 95% confidence interval. Secondary outcomes (i.e., further timepoints and measures) are analyzed along the same line, however from an exploratory viewpoint only; thus, no multiplicity adjustment is required. Where available, observed changes will also be interpreted in relation to published minimally clinically important differences (MCIDs) to evaluate clinical relevance in addition to statistical significance.

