While the study has many strengths in place for the prevention or handling of potential challenges, certain limitations must still be acknowledged. First, since the study involves digital CT, participants must have access to a digital device with a reliable Internet connection and must be capable of using such a device to complete CT. This requirement may exclude some individuals with advanced PD, despite their eligibility based on disease stage. However, an advantage of the digital CT format is that it allows participation from individuals across Germany, including those who are immobile or unable to travel to the research facility. Second, the advanced PD stage may introduce additional challenges. These include disease-related complications, complex medical treatments, fluctuations of motor and non-motor symptoms—potentially affecting the ability to complete CT—and other complications that could impact the study’s progress or lead to a higher-than-expected dropout rate. Moreover, the complexity of care of people with advanced PD may lead to a higher rate of protocol deviations, which must be accounted for. Third, while this study aims to examine a participant pool that more accurately reflects clinical practice, it still excludes individuals with PD who are already suffering from dementia, thus precluding any conclusions on CT in people with PDD. Future research will need to build on this study’s findings to include and investigate individuals with PDD.

Fourth, since participants receive CT together with psychoeducational videos, any observed CT effects must be interpreted as resulting from the combined intervention, as the current study design does not permit separating the effects of CT from those of the psychoeducational component. Further studies using more elaborate statistical designs are needed to isolate specific contributions of each component.

In conclusion, the current study is, to the best of our knowledge, the first large-cohort study examining the effects of CT on people with PD in more advanced disease stages, thus offering class I evidence on the efficacy of digital CT in PD. CT could be an easy-to-administer, far-reaching, and safe intervention to strengthen cognitive functions in this patient group and prevent cognitive decline.

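### The stated 140 randomised, 10% dropout and 64 per group do not quite fit: 140 leaves 63 per group, a minor inconsistency that one restated sentence would settle

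*Protocol article*

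**What the plan says.** The section Sample size {14} of the protocol article gives the design values as follows: "With a power of 80% and a significance level of *p* = 0.05", 64 "participants should be included in each of the two groups". On the effect it says that "a small effect size is expected for global cognitive functions (*d* ≥ 0.3–0.5"). It does not say which value in that range was entered, or whether the test is one- or two-sided.

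It then moves from the requirement to the number randomised: "Considering a dropout rate of 10% [38, 44], the sample calculation provided an overall sample size" of 140, with 70 "persons randomized to either EG or CG". No formula for this step is shown. Trial design {8} confirms equal allocation: "Participants are allocated in a 1:1 ratio to EG and CG".

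The Discussion, among the limitations, adds that advanced disease may bring "other complications that could impact the study’s progress or lead to a higher-than-expected dropout rate".

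**The concern.** An allowance for dropout should make the number left after the expected loss equal to the number that the power calculation requires. Here the requirement, the dropout rate and the number randomised all stand in two adjacent sentences, and the third does not follow from the first two. Taken at its word, the section promises 64 per group with 80% power after 10% dropout, and 70 per group does not deliver that. At stake is the accuracy of a figure that readers will use to judge the trial's power. The mismatch does not depend on the effect size, because it lies only in the step from 64 to 70.

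**Working it through.** **Inputs.** From Sample size {14}: 64 per group (128 in total), 10% dropout, 70 per group (140 in total) randomised, 5% significance level, 80% power, d between 0.3 and 0.5. From Trial design {8}: 1:1 allocation. Sidedness is not stated. I take it as two-sided because the primary contrast is "based on a pairwise contrast of estimated marginal means with a 95% confidence interval" (Statistical methods {20a}).

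**Step 1: reproduce 64 per group.** Two-sample t-test (noncentral t), 80% power, alpha 0.05, n per group rounded up:

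| d | two-sided | one-sided |
|---|---|---|
| 0.3 | 176 | 139 |
| 0.4 | 100 | 78 |
| 0.5 | 64 (63.77 before rounding) | 51 |

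The plan's 64 is matched by d = 0.5, two-sided. A one-sided test would reach 64 somewhere between d = 0.4 and 0.5, but that does not go with a 95% interval.

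**Step 2: what 140 leaves.** Remaining = randomised × (1 − dropout).
- Per group: 70 × 0.9 = 63, against 64 required.
- Total: 140 × 0.9 = 126, against 128 required.

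**Step 3: what 64 needs.** Randomised = required / (1 − dropout).
- Per group: 64/0.9 = 71.1, so 72 per group, 144 in total.
- Rounded on the total: 128/0.9 = 142.2, so 143.
- The stated 140 is 3 to 4 participants lower.

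**Step 4: dropout that 140 can absorb.** 1 − 64/70 = 6/70 = 8.57%, about 8.6%.

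**Step 5: power on completers**, two-sided t-test, alpha 0.05:

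| n per group | d = 0.5 | d = 0.3 |
|---|---|---|
| 63 | 79.5% | 38.6% |
| 64 | 80.1% | 39.2% |
| 72 | 84.6% | 43.2% |

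The row for 72 shows power if nobody were lost. The comparison that matters is 63 against 64: about 0.6 percentage points at either effect size.

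**Step 6: possible origins of 140.** 128 × 1.1 = 140.8, which gives 140 only if rounded down. 63/0.9 = 70 exactly, where 63 is the normal-approximation sample size at d = 0.5. Plain rounding to a convenient total also fits. The article does not allow a choice between these.

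**The case against.** The strongest reply is that the gap has no practical weight. It is one participant per group, and 79.5% rounds to 80%. The planned analysis is also not a t-test on completers. It is an intention-to-treat mixed model with baseline as a fixed effect, and data collected before a dropout are kept unless consent is withdrawn (Plans to promote participant retention {18b}). The 10% is not tied to a visit, and losses between post-test and follow-up take nothing from the primary comparison at T1. If d is scaled to the unadjusted standard deviation (an assumption; the article does not say), baseline adjustment makes up for the missing participant once the baseline–T1 correlation reaches 0.125, since 64 × (1 − 0.125²) = 63.

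Most of this stands, and it fixes the size of the point as minor. It does not remove the inconsistency. The section itself treats 64 as the number needed after loss, and its own dropout rate leaves 63.

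A reader might infer three stronger things, and the document supports none of them:
- *That the authors multiplied by 1.1 instead of dividing by 0.9.* No formula is shown, and other routes lead to 70.
- *That a 14% loss should be assumed, because the feasibility rule accepts training dropout up to 14%.* That limit concerns dropout from training, which only the experimental group can have before post-test. It is not a rate of missing outcomes in both groups.
- *That the limitation in the Discussion shows the allowance to be too small.* It says openly that dropout could exceed expectation. It gives no other rate, and having no reserve beyond the planned rate is not an arithmetic error.

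**Conclusion.** The point holds as a minor inconsistency. At the stated 10% dropout, 140 randomised leave 63 per group and not 64; keeping 64 would take 72 per group, or 143 to 144 in total. This is arithmetic on the section's own figures and rests on no assumption about effect size or test.

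The cost in power is about 0.6 points (80.1% to 79.5%). That figure assumes a two-sided t-test on completers at d = 0.5, with all 10% lost before T1. Losses after T1, or a useful gain from baseline adjustment, would make it smaller still.

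A reader might conclude that the dropout step leaves the trial underpowered. It does not: going from 63 to 64 per group changes almost nothing. Power depends far more on where in the stated range the effect lies. At d = 0.3 it is about 39% with either 63 or 64 per group. For that reason a corrected sentence should not quote power at d = 0.5 alone.

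**What to change.** Keep 140 and restate the sentence in Sample size {14}, for example: *140 randomised (70 per group) leave about 63 per group at 10% dropout; 64 per group is kept up to 8.6% dropout. The calculation assumes d = 0.5 and a two-sided t-test at the 5% level (79.5% power with 63 per group); at d = 0.3, power with 63 per group is about 39%.* The authors should confirm that d = 0.5 and a two-sided test were the values entered, since the article does not state either.

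The cost is wording only. No participants are added and neither design nor analysis changes. Enlarging the trial by 3 or 4 participants would not be proportionate, given that Trial status expected recruitment to be complete by the end of 2025. The stated power becomes slightly less favourable, and its dependence on the effect size becomes visible.

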### Recruitment {15}

Recruitment takes place via the Department of Medical Psychology | Neuropsychology and Gender Studies and the Department of Neurology of the University Hospital of Cologne, Germany. Information on this study is spread nationwide through brochures/flyers, posters, and announcements on the website of the University Hospital Cologne, including the website of the Department of Medical Psychology | Neuropsychology and Gender Studies. Further outreach involves engagement with Parkinson-related networks, associations, self-help groups, and former study participants associated with the Department of Medical Psychology | Neuropsychology and Gender Studies. In case these measures are not sufficient to reach the recruitment goal, various research facilities in Germany can be contacted to support the recruitment process by informing potential participants about the study (i.e., by displaying and/or handing out flyers to potentially eligible people with PD and/or referring potential study participants to the Department of Medical Psychology | Neuropsychology and Gender Studies, so they can be contacted by members of the study team).

## Assignment of interventions: allocation

### Sequence generation {16a}

The allocation sequence was computer-generated with the help of a statistician (author [name]) using the website www.randomization.com. Allocation follows a stratified randomization procedure with permuted blocks of variable length. Participants are stratified by age (< 65 years vs. ≥ 65 years) and cognitive baseline level (*MoCA* ≤ 26 points vs. > 26 points).

### Concealment mechanism {16b}

Allocation lists are securely stored on a password-protected computer drive. Allocation is performed by one of two unblinded supervisory team members (authors [name], [name]), who both have access to the lists but are not involved in neuropsychological assessment. Group allocation is only revealed to participants at the end of their baseline assessment.

### Implementation {16c}

Blinded research fellows and/or trained medicine and psychology student assistants enroll participants and conduct neuropsychological assessments throughout the study. At the end of each baseline assessment and in the absence of the respective examiner, one research fellow (author [name]) receives information on group allocation from one of the supervisory members (authors [name], [name]) and subsequently informs participants about their group allocation. From this point forward, this research fellow (author [name]) is unblinded to all group allocations, and hence does not conduct any post-test or FU assessments, but handles all tasks related to group knowledge, i.e., CT set-up, monitoring of CT progress, leading the video-based consultations, overseeing study progress, and responding to inquiries to the study-specific email. All other examiners remain blinded through assessments and data management.

## Assignment of interventions: blinding

### Who will be blinded {17a}

During baseline assessments, both examiners and participants are blinded. Randomization and group allocation are carried out following baseline assessment by unblinded team members (see Sects. “Concealment mechanism {16b}” and “Implementation {16c}”). Further assessments (post-test and FU) will be carried out single-blinded, i.e., all examiners will be blind to group allocation, while participants are aware of their group. To ensure examiner blinding throughout post-test and FU assessments, participants are reminded prior to every assessment not to give hints on their group allocation. Besides blinded neuropsychological assessments, data management (e.g., data entry, data monitoring) is also carried out in a blinded manner, i.e., all paper-based and digitalized assessment data are pseudonymized and without any information on group allocation (see Sects. “Data management {19}” and “Confidentiality {27}”); therefore, all research fellows and student assistants remain blinded.

### Procedure for unblinding if needed {17b}

No unblinding procedure is planned, as participants are already aware of their group allocation. However, unblinding of the examiners may occur if participants inadvertently reveal their group allocation during neuropsychological assessment (e.g., by asking questions, talking about group allocation, or submitting the CT diary). Incidents of unintentional unblinding are documented, and further assessments are carried out by different, blinded members of the study team.

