## Data collection and management

### Plans for assessment and collection of outcomes {18a}

#### Collection of outcomes

In total, participants will undergo three in-person neuropsychological assessments at baseline, post-test, and 3-month FU (Fig. 2). An overview of all assessments is presented in Table 2. All assessments are conducted in German by experienced research fellows or trained medicine or psychology student assistants. In general, demographic and clinical data (e.g., age, sex, PD duration, concomitant diseases, possible DBS surgery) as well as cognitive reserve measured by the Lifetime of Experiences Questionnaire (LEQ) [72, 73] are collected at baseline only. To control for stable medication treatment, all medication is listed and documented at the beginning of each assessment. This is followed by the neuropsychological assessment. An elaborate test battery with established psychometric instruments was set up to cover cognitive, motor, and further (neuro)psychological outcomes, which may be related to a CT effect. Regarding cognition, at least two tests per cognitive domain are used to allow a level 2 diagnosis of PD-MCI and the exclusion of PDD [103]. Additionally, participants undergo a short motor examination to assess motor outcomes (e.g., severity of motor symptoms, dual-task performance). Short breaks are administered during the assessment as needed. At the end of each neuropsychological assessment, several self-rating questionnaires are handed out to participants to fill out at home and return in a provided pre-addressed, stamped envelope. To assess CT feasibility and acceptability, participants of the EG receive a pen-and-paper CT diary at the end of their baseline neuropsychological assessment. Additionally, technical CT data will be used to assess CT feasibility. The following sections provide an overview of all outcome measures.

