### Data management {19}

Data collection and management will follow the German General Data Protection Regulation. Data is only collected by members of the Department of Medical Psychology | Neuropsychology and Gender Studies. All paper-based data (e.g., informed consent, neuropsychological assessment data, scoring sheets) are stored in locked cabinets at the Department of Medical Psychology | Neuropsychology and Gender Studies in a room with restricted access. Data will be sorted by pseudonymized study ID for easy access during the duration of the study (details on the pseudonymization process are described in Sect. “Confidentiality {27}”). Data acquired on paper will be digitalized by blinded research fellows and student assistants from the study team using SPSS Statistics 29 (IBM Corp., Armonk, NY, USA). SPSS data entry and management is conducted via a dual-control principle according to pre-specified standard operating procedures and is performed continuously during study progress. Each individual step (i.e., data collection and evaluation, digitalization, and monitoring) is documented. The database is saved to a secure server of the Department of Medical Psychology | Neuropsychology and Gender Studies, accessible only through a password-protected computer to members of the study team. Backups are performed regularly. Informed consent forms are stored separately from all other paper-based data in a locked cabinet with restricted access. Digitally acquired data during assessments, i.e., MDS-UPDRS-III videos, are recorded using a standard video camera. Videos are continuously transferred to, saved, and backed up to a password-protected computer and an external encrypted hard drive with restricted access. Scoring of these data is performed by a blinded student assistant not otherwise involved in the study. The scored data is then transferred into the overall SPSS database used for this study. Digitally acquired CT data are stored via the CT program on an external server, inaccessible to members of the study team. Therefore, pseudonymized CT performance data is requested regularly from HelferApp GmbH, Gommern, Germany. Data is saved and stored in a separate data file on a password-protected computer as well as an encrypted hard drive accessible only to one member of the study team (author [name]) and is backed up regularly. Following good scientific practice, all data will be archived and made available upon request for at least 10 years after study completion. No data monitoring committee is used for this study.

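### The diary held only by the training arm is a foreseen route to examiner unblinding, and the stated remedy does not reach a T1 MoCA scored after it surfaces

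*Protocol article*

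**What the plan says.** Under Collection of outcomes {18a}, "participants of the EG receive a pen-and-paper CT diary at the end of their baseline neuropsychological assessment". No diary is described for the control group. The section on feasibility and acceptability outcomes has the diary filled in daily and weekly during training and closed with a final evaluation. The post-test is thus the first scheduled visit at which a completed diary could be handed over.

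Participants know their group; examiners at post-test and follow-up are meant not to (Who will be blinded {17a}). The preventive step stated there is that "participants are reminded prior to every assessment not to give hints on their group allocation". The next section, {17b}, accepts that blinding may still fail during an assessment and lists "talking about group allocation, or submitting the CT diary" among the examples. Its response is: "Incidents of unintentional unblinding are documented, and further assessments are carried out by different, blinded members of the study team".

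The self-rating questionnaires have their own return route: they are "self-rating questionnaires are handed out to participants to fill out at home and return in a provided pre-addressed, stamped envelope". No return route is given for the diary.

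The statistical methods section {20a} makes the T1 contrast in MoCA change the primary comparison, analysed by intention to treat without exclusions.

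**The concern.** The MoCA is scored by an examiner, the comparator is passive and participants are unblinded, so examiner blinding is a main safeguard for the primary contrast. The diary can reveal only one arm. If knowing the arm makes scoring more lenient, this route acts in favour of training and does not cancel between groups. The remedy protects later visits, whereas the primary timepoint is the first visit at which the leak is likely. The trial already has the two things needed to close the route: postal return for its questionnaires, and an unblinded fellow who conducts no post-test or follow-up assessments.

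**Working it through.** **Reading the sections together.** No figure in the protocol bears on this point, so the main check is textual.

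1. Does a diary identify the arm? Yes. Only the experimental group receives one ({18a}).
2. Is hand-over at an assessment foreseen? Yes. {17b} names it.
3. Can it happen at T1? Yes. The diary is complete by the end of training, and T1 is the next scheduled visit.
4. Does the remedy cover the visit under way? As written, no: "further assessments are carried out by different, blinded members of the study team". In {17a} the same expression means the post-test and follow-up visits. On that reading, an incident at T1 changes the examiner from follow-up onwards.
5. Is the affected T1 score treated differently? No re-scoring is described, and {20a} keeps every observation.
6. Must the T1 MoCA be affected? No. The diary has to surface before the MoCA is scored, and the order of tests at T1 is not stated.

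**Illustration of size.** The share of visits affected, the leniency and the SD are assumptions; none is in the documents. The number per arm comes from Sample size {14}. An exact two-sided two-sample t-test with d = 0.5, 80% power and α = 0.05 needs 63.77, so 64 per arm (power 80.1%), which reproduces the stated figure. The protocol does not state sidedness; two-sided is assumed.

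Let p be the share of experimental-group T1 visits scored after unblinding, L the leniency in MoCA points and SD the standard deviation of change.

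- Bias in the group difference = p × L
- Standardised shift δ = p × L / SD
- Noncentrality λ = δ × √(64/2) = 5.657 × δ
- Type I error = probability that a noncentral t with 126 df and noncentrality λ falls outside the two-sided 5% limits

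| | p | L | SD | Bias (points) | δ | λ | Type I error |
|---|---|---|---|---|---|---|---|
| Low | 0.10 | 0.5 | 3 | 0.05 | 0.017 | 0.094 | 5.1% |
| High | 0.30 | 1 | 2.5 | 0.30 | 0.12 | 0.679 | 10.3% |

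The high case equals 0.12/0.3 = 40% of the lower end of the protocol's effect range, and 0.12/0.5 = 24% of the d = 0.5 that yields 64 per arm.

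A second set of assumptions, with 5–30% of visits affected and a shift of 0.2–0.5 SD, gives δ = 0.01–0.15 and a type I error of 5.04–13.6% (normal approximation, 64 per arm). Both ranges start at a negligible value.

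**The case against.** **Data entry.** A reader might infer that the protocol contradicts itself because "Data acquired on paper will be digitalized by blinded research fellows and student assistants from the study team" while {17a} promises that "all paper-based and digitalized assessment data are pseudonymized and without any information on group allocation". The documents do not support that. The promise in {17a} covers assessment data. The examples of paper data in {19} do not include the diary. {16c} gives tasks involving group knowledge to the unblinded fellow, although its list does not name diary collection or entry. Who handles diaries is unsettled, which justifies a request to confirm it and no more.

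**T1 link.** At baseline the MoCA is scored before the other tests. If T1 follows the same order, a diary handed in later in the visit cannot affect it. The wording of the remedy is also not airtight: Participant timeline {13} uses a similar expression for the remaining tests of the same visit. This makes the effect conditional but does not remove it, because no order is fixed for T1.

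**Existing safeguards.** There is a reminder before every assessment, examiners are trained and follow standard operating procedures, and incidents are recorded. These lower the likely frequency. The reminder is general, and the protocol still lists the diary as a residual route.

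**Condensed article.** Diary logistics could sit in procedures that are not shown. That is why the missing return route is not the defect. The point is that a foreseen leak is paired with a remedy that does not reach the primary visit.

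**Keeping the score.** Retaining the observation is what intention to treat requires and is not an error. A sensitivity analysis may be in an analysis plan that is not shown, so its absence is not a finding either.

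**Timing.** Protocol version 6.0 is dated 26 November 2025 and recruitment was expected to end that year, so a change in diary return reaches only the visits still to come. This stands.

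**Conclusion.** The point holds in limited form. The arm-specific diary, its submission at an assessment as an unblinding route, and a remedy directed at later assessments are all in the text. The documents do not show that any T1 MoCA has been or will be scored unblinded, nor that data-entry staff see diaries. Any effect depends on the diary surfacing before scoring, on an unknown frequency and on an assumed direction of leniency. The figures of 0.05–0.30 points and 5.1–10.3% type I error illustrate those assumptions; they are not estimates for this trial. This is a cheap improvement and no threat to the design.

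**What to change.** 1. For all remaining visits, give experimental-group participants a pre-addressed, stamped envelope for the diary, directed to the unblinded fellow. Instruct them not to bring it to T1 or follow-up, and to keep it out of sight when the assessment is at home.
2. State in Data management {19} that this fellow, and not blinded examiners or data-entry staff, receives and enters diary data.
3. Keep the intention-to-treat primary analysis unchanged. Use the incident records that {17b} already requires to flag affected T1 visits, noting whether the MoCA had been scored by then, and repeat the T1 contrast without them as a supportive analysis. Dropping these visits removes mostly experimental-group data on the basis of a post-randomisation event, so the result should be read beside the primary analysis and not in place of it.

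The cost is a revised handout, one envelope per remaining participant, diary entry by the unblinded fellow and one extra analysis. Some diaries may arrive late or be lost. This would fall mainly on the acceptability ratings, which come from the diary alone; feasibility data also come from the training software.
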